#### Participants

Participants will include 300 parents/caregivers (150 from Fairfield Local Government Area (LGA) and 150 from Murrumbidgee Local Health District (LHD)) of children aged 6 months to 3 years (inclusive).

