#### Setting

Fairfield (population: 198,817; 102 km^2^) [24] is an urban area and has a high proportion of CALD families, with about 70% of residents speaking a language other than English at home [24]. Murrumbidgee LHD (population: 77,652; 125,242 km^2^) [24] is considered mostly regional with one remote area making access to health care a challenge for most families with young children.

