##### Randomisation

Upon completion of the consent forms and Time 1 questionnaires, families will be randomised to either the intervention or CaU group. Computerized randomisation software will be used to create a randomisation table via REDCap (a secure web application for building and managing online surveys and databases) [25]. Participants will be assigned randomly to each arm ensuring a 50:50 ratio.

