##### Statistical analysis

A multilevel models estimated by restricted maximum likelihood (REML) with logit link function will be used to model service utilisation over the 3 time points. The main predictors of interest will be time, group and a time by group interaction which will compare service utilization between the groups at each time point. The analysis will be adjusted for the caregivers, socioeconomic status, and the main language spoken in the home.

A multilevel model estimated by restricted maximum likelihood (REML) with identity link function will be used to model the K10, WE CARE and LTSAE totals. The main predictors of interest are time, group and time by group interaction. The analysis will be adjusted for the caregivers, socioeconomic status, and the main language spoken in the home.

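### Site is a fixed recruitment quota and plausibly prognostic, but the stated covariate list omits it and includes an entry that is not a collected variable (minor)

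*Protocol article*

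**What the plan says.** Under Participants, the article fixes the sample by site: "150 from Fairfield Local Government Area (LGA) and 150 from Murrumbidgee Local Health District (LHD". Under Setting, it describes two different places. Fairfield "is an urban area and has a high proportion of CALD families", with about 70% of residents using another language than English in the home. Murrumbidgee "is considered mostly regional with one remote area making access to health care a challenge for most families with young children".

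Under Randomisation, it says that "Computerized randomisation software will be used to create a randomisation table via REDCap" and that "Participants will be assigned randomly to each arm ensuring a 50:50 ratio". No stratum is named, and none is ruled out.

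Under Statistical analysis, the service-utilisation model is specified thus: "The main predictors of interest will be time, group and a time by group interaction". The article adds that the interaction serves to compare the groups time point by time point. The covariates are then listed: "The analysis will be adjusted for the caregivers, socioeconomic status, and the main language spoken in the home". The same list is given again for the K10, WE CARE and LTSAE totals. Site is in neither list, and no site level is named for either multilevel model.

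**The concern.** Site is a design factor here: its distribution is set in advance, it is known for every family before randomisation, and the article itself says that access to care is difficult in one of the two places. Service use is the outcome on which the trial is sized, so site is plausibly prognostic. Home language is only a partial substitute. It cannot separate an English-speaking family in Fairfield from one in Murrumbidgee, although distance to services and their supply may differ.

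The list also has an entry that cannot be run as written. The demographic questionnaire described under Assessments collects parental age, education and country of birth, marital status, socioeconomic status and home language, among other items, but nothing called caregivers. It may be a lost word, or a possessive belonging to socioeconomic status.

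At stake is precision, and protection against a chance difference in site mix between the arms. The validity of the trial is not at stake.

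**Working it through.** **Plan's own figure.** Inputs from Sample size calculations: 244 families (122 per arm), 30% v 60%, 5% significance, taken as two-sided.
- Null SE = √(2 × 0.45 × 0.55 / 122) = 0.0637. Alternative SE = √((0.21 + 0.24) / 122) = 0.0607.
- z = (0.30 − 1.96 × 0.0637) / 0.0607 = 2.88, so power is 99.8%. This agrees with the stated figure of more than 99%. With 150 per arm it is above 99.9%.

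**Chance imbalance if allocation is not stratified.** Inputs: 150 families per site (Participants) and 150 per arm (Sample size calculations).
- The number of Fairfield families in one arm is hypergeometric(300, 150, 150), with SD = √(150 × 0.5 × 0.5 × 150/299) = 4.34.
- SD of the between-arm difference in site share = 2 × 4.34 / 150 = 5.8 percentage points.
- A difference of 10 points or more means 67 v 83 of 150 or worse (16/150 = 10.7 points). Its probability is 8.3%. For 15 points or more it is 0.8%.
- With an assumed site gap of 20 points in service use, 67 v 83 moves an unadjusted estimate by 0.107 × 20 = 2.1 points. The planned effect is 30 points, and the SE of the risk difference is √(0.45/150) = 5.5 points.

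**Precision at one time point, no other covariates.** The article gives no service use by site, so the gap d is assumed. Without site, the variance is proportional to 0.21 + 0.24 = 0.45. Within sites each arm loses d²/4, so it becomes 0.45 − d²/2. Gain = 0.45 / (0.45 − d²/2) − 1.

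| Assumed site gap | Variance term using site | Efficiency gain |
|---|---|---|
| 0 points | 0.450 | 0% |
| 10 points | 0.445 | 1.1% |
| 20 points | 0.430 | 4.7% |
| 30 points | 0.405 | 11.1% |

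For a continuous total with an assumed standardised site difference s, the gain is s²/4: 1% at 0.2 and 6% at 0.5.

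**Power and type I error.** Single-time-point logistic models were simulated with 300 families and 1,500 runs per setting (Monte Carlo error about 1 point where power is near 77%).
- At 30% v 60%, power was above 99.9% with or without site.
- At an assumed smaller effect of 30% v 45%, power without and with site was 77% and 77% at no gap, and 75% and 77% at a 20-point gap.
- Type I error was 4.1% to 5.6% over all settings, and 4.7% to 5.6% in the models without site.

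**The longitudinal model.** The answer depends on which contrast is read from it.
- Change from baseline (the interaction coefficient): a stable site difference is already present at Time 1 and nearly cancels. In simulation the mean z was 2.005 without site and 2.008 with it.
- Groups at a given time point, which is the purpose the article states: with a log-odds site gap of 1.0 (odds ratio e^1.0 = 2.7), mean z rose from 2.49 to 2.58. With a gap of 1.8 (odds ratio e^1.8 = 6.0), it rose from 2.38 to 2.56. There was no gain at zero gap.

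In a logit model this gain does not come from a smaller standard error for the coefficient. It arises because the odds ratio conditional on site lies further from 1.

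**The case against.** The strongest case against the point is that the planned model contains baseline, so a stable site effect drops out of the time-by-group interaction and a site term would change almost nothing. That stands for the change-from-baseline contrast. It does not dispose of the point, because the article says the interaction is there to compare groups at each time point, and for that contrast a modest gain remains.

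Second, the size rests on an assumed gap. Both communities are described as disadvantaged, so the gap in service use could be small, and at zero gap nothing is lost. Home language is already in the model and carries part of the site information. This also stands, and it puts the likely gain toward the lower end of the range.

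A reader might go further than the article allows in four ways.
- That randomisation is unstratified. The article does not say so, and a condensed article may leave strata and block sizes to the full protocol. If allocation is in fact stratified by site, a model without site gives slightly conservative tests, so the covariate change is sensible either way.
- That site is the strongest predictor of service use. No figure by site is given, and the Discussion names cultural and linguistic barriers alongside geographic ones.
- That the omission biases the result or leaves the trial underpowered. The calculations show neither.
- That risk level should also be a stratum and a covariate. It is built from the Time 1 K10, WE CARE and LTSAE responses, which are also the first outcome measurements in the second model, and nothing here supports adding it.

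The absence of a planned site-by-group estimate is ordinary analysis-plan content and is not a fault of the article.

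**Conclusion.** The point holds in a limited form and is minor. The article spells out its covariates twice, omits a baseline factor that its own design fixes, and includes an entry that matches no collected variable. The cost is an efficiency loss of about 0% to 11% in the comparison at a single time point, for assumed site gaps of 0 to 30 points and before language adjustment, which reduces it. The effect on the change-from-baseline interaction is close to nil. The 8.3% chance of a site imbalance of 10 points or more applies only if allocation is unstratified, and assumes exactly 150 families per site and per arm. Type I error, and power at 30% v 60%, are not affected.

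**What to change.** Add site as a fixed effect in both models under Statistical analysis; two sites are too few to estimate a random effect. Replace the caregivers entry with the collected variable that was meant, or, if it was a possessive, join it to socioeconomic status. Make both changes before comparative outcome data are seen. It would also help to state whether the allocation table is stratified by site. Site-specific effects may be reported descriptively.

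The cost is one degree of freedom per model. The odds ratio for service use also becomes conditional on site, which the report should say.

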##### Economic analysis

Economic evaluation will assess the cost effectiveness (cost utility) of the intervention against usual care. Costs will include the care coordinator for the intervention group and the costs of completed service referrals for both trial arm. Effectiveness will be measured by converting K-10 scores into utilities using a mapping algorithm that converts scores to EQ-5D values [29]. REML will also be applied to assess significant changes in costs and outcomes. An Incremental Cost Effectiveness Ratio (ICER) will then be generated with values $42,000–$67,000 considered to be cost effective [30]. Implementation costs from roll-out will be estimated, including the eligible population size, the number of service coordinators required and service referrals. Sensitivity analysis will then vary key parameters such as service uptake and a threshold analysis will estimate the minimum service engagement required to maintain cost effectiveness in implementation. A value of information analysis will estimate statistical uncertainty and the potential value from further research to optimize implementation.

### Phase 2: implementation evaluation

#### Design

Semi-structured one-on-one qualitative interviews lasting between 30 to 60 min will be conducted with participants and stakeholders via telephone or video call. Participants not proficient in English will have access to interpreters.

#### Participants

Participants will include approximately 30 families who participated in the study (15 from the CaU group and 15 from the intervention group) and 30 key stakeholders (e.g., CFHN, service providers, policy makers).

#### Recruitment

Participants in the wider RCT will be asked to indicate their consent on the RCT consent form to being contacted regarding participation in the qualitative component of the study. Those who indicate ‘yes’, will be contacted directly by a researcher after the RCT 12-month follow-up. Furthermore, the study will be advertised via flyers posted at participating sites in both Fairfield LGA and Murrumbidgee LHD and all RCT participants and stakeholders will be emailed the flyer.

#### Data collection and analysis

Participants who have indicated that they wish to take part in the interview will be contacted via email by a researcher to arrange an interview date and time. Once arranged, the researcher will email participants an information sheet and consent form. The research officer will then contact participants via telephone or video call at the scheduled time. Prior to the interview, the research officer will review the information sheet with the participant, ensuring that the consent form has been signed and returned.

The semi-structured interviews will be theoretically framed using the Consolidated Framework for Implementation Research [CFIR] and will consider barriers and facilitators for effective rollout. In addition, we will assess key implementation metrics including acceptability, adoption, appropriateness, fidelity, coverage, and sustainability [31–33]. Interviews will be digitally recorded, transcribed verbatim, and thematically analysed with an iterative framework analysis using NVivo Pro 12 software.

### Data storage and record retention

All participant data collected through REDCap will be stored securely on University of New South Wales REDCap servers which are password protected. All interview recordings and operational trial data (e.g., hard copies of flyers, ethics documentation) will be stored electronically on the Southwest Sydney Local Health District password-protected network drives which are accessible to a small number of Chief Investigators. No external personnel will have access to the data. The electronic data and paper files will be kept for 25 years, and the database will be deleted at the end of this time.

### Management of the project/governance

The clinical governance of the project (shown in Fig. 3) will be established through a top-down level framework. Firstly, the Project Steering and Evidence Translation Committee (highest-level) will be overseeing the Child and Family Health Services at the state level of NSW. This steering committee will include chief investigators, senior executives, and clinical stream leaders from each site (Fairfield and Murrumbidgee), partner organisations and consumer representatives, and will convene quarterly to oversee and guide the study. Secondly, a research and implementation committee, comprised of all academic researchers, clinicians, and project staff, will support the Project Steering and Evidence Translation Committee and will be convened bi-monthly to manage study execution. Research site groups (Fairfield and Murrumbidgee) will be responsible for the daily operation of the study, including collecting, assessing, reporting, and managing solicited and spontaneously reported adverse effects. As this study does not involve any investigational therapeutic goods or devices, all adverse events and other unintended effects of trial intervention or conduct will be reported to the relevant authorities as per the principles of the NHMRC National Statement on Ethical Conduct in Human Research guidelines [34]. This information will also be reported to the Data Monitoring Committee (DMC) and included as part of the project’s annual progress report to the relevant ethics committee.

**Fig. 3 Fig3:**
[figure not shown]
WMG-E Clinical Governance Framework

An independent DMC comprising of experts in clinical trial conduct in health services research, statistics, mental health, and child development will meet once every 6 months to monitor the quality of the trial data and safety of research participants. DMC will monitor blinded response variables and safety outcomes for early dramatic benefits or potential adverse events and provide reports to the investigators on recommendations to continue or temporarily halt recruitment to the study. The committee will be governed by a charter that will outline their responsibilities, procedures, and confidentiality.

### Auditing

The study may be audited by the South Western Sydney LHD ethics committee and inspected by government regulatory authorities. Any source information and other study files will be made accessible at all study sites (SWSLHD and MLHD) at the time of auditing and inspection during the course of the study and after the completion of the study.

## Discussion

Families from disadvantaged backgrounds face a fragmented health system with financial, social, and structural barriers. Even when services are available, engagement and access to services are compounded by cultural and linguistic barriers as well as geographic challenges. These are exacerbated by the pandemic and the consequent impact on in-person services.

This study will address these challenges by testing the WMG-E web-app as a digital navigation tool to engage parents at home or through opportunistic contacts with health, early childhood education or other community/social care services. Extending earlier research using WMG-E to engage parents in developmental monitoring [35], this study will include parental mental health and psychosocial needs, alongside child developmental needs. Thus, this study will test the acceptability, effectiveness, and cost-effectiveness of WMG-E for families of children aged 6 months to 3 years (inclusive) in a predominantly CALD community and a regional/rural community to increase engagement of families with services and better identification of their needs.

Furthermore, this study will specifically evaluate whether a service navigator will increase family wellbeing by facilitating access to relevant services. Families in the intervention group are expected to experience significantly improved parental mental health, psychosocial wellbeing, and development outcomes compared to the control group. By targeting CALD and rural/regional communities, we will demonstrate the feasibility of the WMG-E for the most vulnerable and disadvantaged families. Following this, the online platform will be ready for national implementation with potential for international adaptation.

### Impact on policy and practice

If findings provide evidence that engaging parents in mental health, psychosocial, and developmental screening via an electronic platform improves parental engagement and access to services, the study will have significant practice and policy implications for supporting vulnerable families. Moreover, the study will serve to clarify the factors that help and hinder the implementation and sustainability of a digital tool within routine services using opportunistic contacts with families. Specifically, by exploring the five domains of the CFIR (intervention characteristics, inner/outer settings, characteristics of individuals involved in implementation and process [36, 37]), we will ascertain the acceptability and cultural appropriateness of the tool, as well as barriers that hinder adoption. This will generate the evidence needed to evaluate the factors influencing program implementation at scale.

### Limitations

Due to the nature of the intervention, it is not possible for participants or service navigators to be blinded to study conditions. Furthermore, the services that participants are connected with will vary depending on their needs. It will therefore be difficult to determine whether improved outcomes are due solely to the service navigator, the service attended, or a combination of both.

## Data Availability

Not applicable.

## Abbreviations

CALD: Culturally and linguistically diverse
CaU: Care-as-usual
CDC: Centre for Disease Control
CFHN: Child and Family Health Nurses
GPs: General Practitioners
ICER: Incremental Cost Effectiveness Ratio
K10: Kessler Psychological Distress
LGA: Local Government Area
LHD: Local Health District
LTSAE: Learn the Signs Act Early
NGOs: Non-governmental organisations
NSW: New South Wales
QR: Quick response
RCT: Randomised Controlled Trial
RELM: Restricted maximum likelihood
WMG-E: Watch Me Grow – Electronic Platform
